**Figure 4 F4:**

Visual analog scale.

**Table 2 T2:**
[figure not shown]
Presentation of the Likert-type scale.

### Adverse events and complications

2.12

The participants of this study should voluntarily report information regarding adverse events to researchers (e.g., pallor, fainting during acupuncture treatment, sweating, dizziness, local hematoma, bleeding, unbearable prickling, as well as continuous severe pain more than 1 h after acupuncture). The adverse events regarding the acupuncture (e.g., sticking of the needle, broken needles, and bent needles) will be reported by acupuncturists. All adverse events should be completely registered on the adverse events page of case report forms (CRFs). Researchers are supposed to ascertain the occurrence of adverse events while recording all details (e.g., date, time, extent, and correlation with treatment). Data on postoperative complications will be recorded during hospitalization and within 2 weeks after discharge, any complications that will threaten the life of the subjects, or serious adverse events will be also recorded. The researchers will seek emergency medical assistance and report the serious adverse events immediately.

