## Introduction

1

Postoperative gastrointestinal dysfunction (PGD) refers to a common postoperative complication, capable of causing many clinical symptoms (e.g., nausea, vomiting, abdominal pain, bloating, constipation, as well as diarrhea).^[1]^ PGD is likely to cause intestinal paralysis, acute gastric dilatation, and obstructions in severe cases, thereby affecting patients’ quality of life and prolonging the hospital stay of the patient.^[2]^ The specific mechanism of PGD remains unclear. It has been known that PGD is tightly associated with general anesthesia, gastrointestinal hormones, electrolyte disturbance, as well as abdominal inflammation.^[3]^ For the routine treatment of PGD, fasting, enema, oxygen inhalation, analgesia, fluid supplement, acid–base regulation, infection prevention, as well as gastrointestinal decompression are covered.^[4]^ Granisetron, domperidone, cisapride, and everypan refer to the typical drugs for PGD. Domperidone and cisapride are likely to induce adverse reactions of cardiovascular system; granisetron can cause fever and headache, and side effects of nausea and vomiting may be attributed to evermopan.^[5]^ As reported in the mentioned literature, the side effects and potential risks of these drugs limit their wide application.

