### Intervention

2.10

The treatment strategy of this study will be collectively formulated by experienced acupuncturists, surgeons and anesthesiologists. After laparoscopy, all the subjects will be fasted and in supine position without pillow, the intervention is going to be conducted once 30 min after surgery. The experimental group will receive the treatment of sterile disposable stainless-steel needles (*Huatuo* medical instruments Co. Ltd., Suzhou, China; 0.3 mm × 40 mm/0.3 mm × 25 mm). Acupoints will be located abiding by the World Health Organization Standard Acupuncture Point Locations in the Western Pacific Region.^[32]^ The fixed prescription includes *Hegu* (LI4), *Neiguan* (PC6), *Zusanli* (ST36), *Gongsun* (SP4), lateral line 2 of forehead (MS3), lateral line 3 of forehead (MS4), and middle line of vertex (MS5) (Fig. 3), all acupoints will be bilaterally selected except for middle line of vertex (MS5). The acupuncture needles will be inserted into acupoints after the routine sterilization; subsequently, it will be evenly lifted, inserted and then twisted to *Deqi* after reaching the standard depth; the operation of each acupoint will take 30 s. The needles will be maintained on the trunk and limbs for 30 min and on the head for 6 h after *Deqi*. Acupuncture will be performed by two acupuncturists registered in China and with over 3 years of clinical experience. They will receive the relevant training before the experiment, the training courses covered acupoint positioning, acupuncture operation skills and communication skills. The control group will be intervened by professional surgical nurses, the treatment will be intravenous injection of granisetron with 3 mg/3 mL (drug approval No. H20030161, Sichuan Taiji Pharmaceutical Co., Ltd).

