#### Statistical analysis

2.15.2

1.Analysis procedures sample distribution: The number of dropouts and the rate will be described and analyzed for each data set, and the reasons for any dropouts are elucidated.2.Balance comparison: The subjects’ general data will be compared to assess the comparability of the two groups.3.Efficacy analysis: The subjects’ time to first flatus will be used as the primary outcome measure to assess the efficacy and safety of acupuncture in treating PGD. The means (χ) and standard (SD) deviations will be calculated to express the outcome measure, and the experimental and control groups will be statistically compared by two independent-sample *t* tests. Eight secondary outcomes will be applied to assess the efficacy of the acupuncture. Seven of these—namely, time to first defecation, abdominal pain, dosages of analgesia pump, abdominal distention, nausea, vomiting, and gastrointestinal hormones will be described usinḡχ± SD deviation and statistically compared between groups by Repeated Measures Analysis of Variance (RMANOVA). The statistical analysis of time to first defecation will be identical to that of time to first flatus. However, before performing RMANOVA, a sphericity test will be performed to determine whether the data are suitable for analysis by RMANOVA. If the data do not conform to the conditions of sphericity condition, the degree of freedom will be corrected using factor ε before the RMANOVA is performed. The categorical measure of psychological status will be analyzed using either the rank-sum test or Spearman's rank correlation.4.Safety analysis: In accordance with the definition of adverse events, specific adverse events, their severity level, causes, and explanations will be listed. The number of adverse events, and the incidence of adverse event will be statistically described. If inter group comparison is required, the χ^2^ test or Fisher's exact test will be performed.5.Methods of statistical analysis: An independent statistician analyzed the outcome data in accordance with the principle of intention-to-treat (ITT), that is, all subjects recruited in the group will be covered. The analysis of efficacy and safety indicators will be conducted following the principle of per-protocol (PP), that is, all subjects who completed the whole trial process without major protocol violations will be included. All statistical analysis complied with ITT population, and the results of ITT analysis will be compared with PP analysis to assess the sensitivity. All missing data will be analyzed using the last observation carried forward (LOCF) interpolation method. The qualitative data will be tested for normality, according to which independent *t* test or Mann–Whitney *U* test will be performed for groups comparison. Qualitative variables will be presented by the statistical description of χ ± SD of the normal distribution data, whereas qualitative variables will be recorded as the number of cases in each category. If the quantitative variables constitute repeated measures data, RMANOVA will be adopted for comparison, and the sphericity test will be performed to ascertain the applicability of, as well as to correct the data. The categorical variables will be represented by numbers (percentages) by χ^2^ test or Fisher's exact test *P* < .05 will be considered statistically significant on both sides in all the statistical tests. SPSS 25.0 software (SPSS, SPSS Inc, Chicago, IL) will be adopted for data statistical analysis.

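### Adverse events are collected by voluntary report, with examples and a named staff reporter that lean to the acupuncture arm, so the safety comparison is open to ascertainment bias of unknown size and direction

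*Protocol article*

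**What the plan says.** **Source of reports.** Section 2.12 (Adverse events and complications) states: "The participants of this study should voluntarily report information regarding adverse events to researchers". The examples that follow are "pallor, fainting during acupuncture treatment, sweating, dizziness, local hematoma, bleeding, unbearable prickling, as well as continuous severe pain more than 1 h after acupuncture", introduced as an open list.

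**Staff reporter.** The same section adds: "The adverse events regarding the acupuncture (e.g., sticking of the needle, broken needles, and bent needles) will be reported by acupuncturists". Section 2.10 (Intervention) says of the other arm: "The control group will be intervened by professional surgical nurses". No adverse-event role is stated for those nurses.

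**Provisions common to both arms.** Section 2.12 also says: "Researchers are supposed to ascertain the occurrence of adverse events while recording all details". It has every event entered on the adverse-event page of the case report form (CRF), and complications recorded in hospital and for 2 weeks after discharge.

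**Known effects of the comparator.** The Introduction says "granisetron can cause fever and headache". Neither effect is among the examples in section 2.12.

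**Analysis.** Section 2.15.2, item 4: "The number of adverse events, and the incidence of adverse event will be statistically described". A chi-squared or Fisher's exact test follows only if a comparison between groups is needed. Section 2.8 accepts that neither participants nor acupuncturists can be fully blinded.

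**The concern.** Safety is part of the stated aim, and the rationale is comparative: the Introduction argues that side effects limit the use of the available drugs. The safety data therefore have to show how the two treatments compare.

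The chance that an event is recorded depends on whether anyone thinks to mention it. Here the person reporting usually knows the treatment, the examples point mostly towards one treatment, and only one arm has a named staff reporter. A difference in recorded incidence, or the absence of one, could then reflect reporting and not the treatments. Side-by-side descriptive percentages have the same weakness as a formal test. Events that were never elicited cannot be recovered at the analysis stage.

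**Working it through.** **1. The stated provisions, arm by arm**

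| Element | Acupuncture | Granisetron |
|---|---|---|
| Participant report (2.12) | voluntary, not fully blinded | voluntary, not fully blinded |
| Examples (2.12) | two of eight name acupuncture; haematoma and prickling are needle-type | pallor, sweating, dizziness and bleeding can occur in either arm; fever and headache absent |
| Named staff reporter | acupuncturist (2.12) | none stated for the nurses (2.10) |
| Researcher ascertainment, complications (2.12) | yes, no method of asking given | yes, no method of asking given |

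The first and last rows are the same in both arms. The asymmetry lies in the two middle rows.

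**2. What unequal capture would do**

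The article gives no adverse-event rate and no power for safety, so there is no figure of its own to reproduce.

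Inputs from the article: 90 per arm (2.1); two-sided 0.05 and Fisher's test (2.15.2).

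Assumptions, not in the article: the same true incidence *p* in both arms, and a share *c* of events captured in each arm.

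Observed incidence = *p* × *c*. The apparent risk ratio is the ratio of the capture shares. For *p* = 20% and capture of 90% v 70%, observed rates are 0.20 × 0.90 = 18% and 0.20 × 0.70 = 14%, that is 16.2 v 12.6 expected patients. The apparent risk ratio is 0.90/0.70 = 1.29 although the true ratio is 1.

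The probability of P < 0.05 comes from enumerating all pairs of binomial counts. Both directions are included:

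| Capture, acupuncture v granisetron | Apparent risk ratio | *p* = 10% | *p* = 20% | *p* = 30% |
|---|---|---|---|---|
| 90% v 90% | 1.00 | 2.9% | 3.2% | 3.4% |
| 90% v 70% | 1.29 | 4.7% | 7.9% | 11.8% |
| 90% v 50% | 1.80 | 11.6% | 27.3% | 44.0% |
| 70% v 90% | 0.78 | 4.7% | 7.9% | 11.8% |

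In the second and third rows nearly all false positives show an excess with acupuncture. In the last row they show an excess with granisetron.

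**3. What counting needle-only events would do**

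This is a separate mechanism. Assume full capture and a shared-event incidence of 10%, and add events that only needling can cause in a share *e* of acupuncture patients. The acupuncture rate becomes 1 − (1 − 0.10)(1 − *e*): 11.8%, 14.5% and 19.0% for *e* = 2%, 5% and 10%. Fisher's test then shows a significant excess with acupuncture in 3.8%, 10.8% and 33.3% of trials. These are real events, so this is not under-detection in controls. It shows that an any-event comparison depends on whether needle-only events are counted.

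**The case against.** A reader might infer that the trial relies on voluntary report alone, that only acupuncture events are prompted, and that the safety comparison is therefore biased. The article does not support that reading, for five reasons.

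- Section 2.12 also has researchers ascertain events and record complications in both arms. This stands as mitigation. It does not remove the point, because no shared way of asking is described, and the sentence can be read as documenting events already reported.
- The examples are an open list, not a checklist read to patients, and several could occur in either arm. Nothing says the arms are asked different questions. What stands is that the list leans one way and omits the comparator's effects that the article itself names.
- The acupuncturists' stated examples (stuck, broken or bent needles) cannot happen with granisetron. The extra reporter therefore mainly affects which events belong in a comparison. It does not show that shared events are missed in controls.
- The between-arm test is conditional, and the main plan is to list and describe events. The incidences are still described for a comparative purpose.
- The full protocol and CRF are not shown, and symptom questions may sit there. The missing fever and headache items do not prove that the CRF lacks them. The point rests on the collection rule the article does state.

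The larger false-positive rates in the table depend wholly on assumed capture shares and are not evidence of what will happen in this trial.

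**Conclusion.** The point holds in limited form. The stated collection rule is not symmetric between arms, and the provisions common to both arms do not fix a common method. The adverse-event incidences, and any test built on them, are open to ascertainment bias. The article does not establish that they are biased, by how much, or in which direction. Unblinded patients could under-report in either arm.

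A moderate imbalance, 90% v 70% capture with equal true incidence of 10% to 30%, would raise the false-significance rate from about 3% to between about 5% and 12%. That range is an illustration and rests on those assumptions. The weakness concerns the safety conclusion only and does not touch the primary efficacy result. It is worth correcting before data collection because it cannot be repaired afterwards.

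**What to change.** - **Ask both arms the same questions.** Add one short structured adverse-event enquiry to the CRF, used at the existing t1 to t5, discharge and 2-week contacts. Cover expected effects of both treatments, such as dizziness, sweating, headache and fever, and end with an open question.
- **Protect the evaluator's blinding.** A patient answering an open question may mention needles. Have existing research staff other than the blinded evaluator ask it, or ask it only after that contact's efficacy ratings are recorded.
- **Keep efficacy symptoms out.** Leave out constipation and diarrhoea: the Introduction lists them as symptoms of postoperative gastrointestinal dysfunction, so they belong with efficacy.
- **Define what is compared.** Base any between-arm comparison on the events asked about in both arms. Tabulate needle-specific events (stuck, bent or broken needle, needle-site haematoma) descriptively for the acupuncture arm only.

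Cost: one CRF page and a few minutes per contact, at visits already scheduled. More minor events will be recorded, and the order of questioning needs care to keep the evaluator blinded.

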### Data collecting and monitoring

2.13

The result data of this study will be recorded by a special evaluator on the paper CRF. To more effectively conduct the observation of indicators and data collection, the CRF contained all information (e.g., observation time, observation indicators, adverse event records, as well as safety assessment). The result evaluator should fill in the relevant information quickly and accurately in accordance with the principle of CRF. The evidence-based medicine center of Chengdu University of TCM will be responsible for data monitoring every 3 months. The acupuncturists and statisticians cannot access or obtain the data during the whole assessing process.

### Quality control

2.14

To ensure the quality of the study, methodology experts, acupuncturists, surgeons, and anesthesiologists discussed and revised the protocol repeatedly. Before the launching of the project, all researchers must receive unified training covering research scheme, test process, operation specification, etc. The quality controller directly appointed by the project leader will check the CRF every 2 weeks. The original data on the CRF cannot be modified. If it needs to be modified, the reason for the modification shall be stated, and the name of the modifier shall be written next to the modification. The conference will be held by researchers every 3 months to report and discuss the process of the study.

### Sample size and statistical analysis

2.15

#### Sample size calculation

2.15.1

The total sample size of the study will be calculated by the formula based on a two-group, parallel, controlled design: n = (*Z*_1−*α*/2_ + *Z*_1−*β*/2_)^2^ × (*σ*2 1 + *σ2 2*)/*δ*^2^, where n denotes the sample size of each group, *σ* represents the standard deviation, and δ indicates the clinical significance between groups. At an α = 0.05, power = 80%, and given a bilateral test, *Z* scores of *Z*_1−*α*/2_ = 1.96 and *Z*_1−*β*/2_ = 0.84 will be obtained from the *Z* score table. Eighteen subjects recruited from February 2018 to March 2018 will be recruited in the pilot trial, and the primary outcome measure will be the time to first flatus: S1 = 2.21 and S2 = 3.53. Based on preliminary trial and clinical experience, the reduction of 4 h in the time to first flatus will be defined as our clinical expectation. Accordingly, the rounded sample size in each group is n ≈78. Assuming that the dropout rate is 15%, 180 subjects (90 in each group) will be needed in the two groups.

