
Some systematic reviews have also verified the feasibility of acupuncture for PGD and have drawn a positive conclusion.^[22,23]^ For the defects of research quality, statistics and research methods, the clinical results should be interpreted rigorously, and their scientific basis remain insufficient.^[24]^ Scalp acupuncture is a part of acupuncture therapy to treat diseases by stimulating specific location of the head area, showing a considerable effect on numerous diseases resulting from the brain.^[25]^ The acupuncture prescriptions for PGD primarily involve the points located in trunk and limbs.^[26]^ In the present clinical trial, the acupoints in the head area will be chosen in accordance with brain-gut axis theory, which is a novel exploration and attempt to apply acupuncture for PGD. By referencing to the design of similar studies,^[27]^ 18 patients having undergone laparoscopic surgery were pre-tested strictly following the evaluation and treatment process of this study. These subjects were randomly classified to “experimental group” (acupuncture) and “control group” (granisetron); the experimental group (16.31 ± 2.21 h) had a shorter average time to first flatus than the control group (26.14 ± 3.53 h). According to the preliminary results, acupuncture can effectively relieve gastrointestinal dysfunction after laparoscopic cholecystectomy.

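### The stated sample-size formula and inputs give 9 patients per group, not 78; the dropout step to 90 also falls slightly short of its own target.

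*Protocol article*

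**What the plan says.** Section 2.15.1 of the protocol article sizes the trial with a two-group formula for comparing means, "where n denotes the sample size of each group". The inputs are all given:

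- Error rates: "At an α = 0.05, power = 80%, and given a bilateral test", with Z values of 1.96 and 0.84. The second quantile carries the subscript 1−β/2.
- Variability, from an 18-patient pilot: "the primary outcome measure will be the time to first flatus: S1 = 2.21 and S2 = 3.53".
- Difference: "the reduction of 4 h in the time to first flatus will be defined as our clinical expectation".

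The result is stated as "Accordingly, the rounded sample size in each group is n ≈78". The last step is "Assuming that the dropout rate is 15%, 180 subjects (90 in each group) will be needed in the two groups".

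The Introduction reports the same pilot with the same spread: "the experimental group (16.31 ± 2.21 h) had a shorter average time to first flatus than the control group (26.14 ± 3.53 h"). Sections 2.1 and 2.7 repeat 90 patients per group.

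**The concern.** The paragraph presents a complete calculation whose result does not follow from it. This is not a detail that an article leaves to a fuller document, because the formula, the inputs and the answer are all printed and disagree.

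This is the only justification given for enrolling 180 patients. As it stands, a reader cannot tell what the trial is powered to detect. If the SDs are as stated, the trial is far larger than 4 h requires, and differences well below 4 h will be statistically significant. If the true basis was a larger SD or a smaller difference, that basis is not reported and cannot be checked.

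**Working it through.** **Inputs** (section 2.15.1; the SDs also appear in the Introduction): Z = 1.96 and 0.84; S1 = 2.21 h; S2 = 3.53 h; δ = 4 h; n per group; allocation 1:1 (section 2.1).

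**1. The plan's own formula.** n = (1.96 + 0.84)² × (S1² + S2²) / δ²

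- (1.96 + 0.84)² = 7.84
- 2.21² + 3.53² = 4.884 + 12.461 = 17.345
- n = 7.84 × 17.345 / 16 = 8.50, so **9 per group**

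The plan says 78, and 78 / 8.50 = 9.2. The stated figure is not reproduced.

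**2. Does any variant give 78?**

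| Variant | n per group |
|---|---|
| Exact t test (power 0.772 at 9, 0.819 at 10) | 10 |
| Inflation for a Mann–Whitney test | about 10 |
| One-sided test | 7 |
| Second quantile taken as labelled, Z(1−β/2) = 1.28 | 12 |
| Larger SD in both groups | 13 |
| 95% power | 15 |
| 99% power | 20 |
| (S1 + S2)² in place of S1² + S2² | 17 |
| Result doubled to a total | 17 |
| δ not squared | 34 |
| Observed pilot difference, 26.14 − 16.31 = 9.83 h | 2 |

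None comes near 78.

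**3. What inputs would give 78?**

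- Difference, with the stated SDs: √(7.84 × 17.345 / 78) = 1.32 h.
- Common SD, with 4 h: √(78 × 16 / (2 × 7.84)) = 8.92 h. The pilot equivalent is √(17.345 / 2) = 2.94 h, so this is a 3.03-fold inflation.
- Allowing for pilot imprecision: if the 18 pilot patients were split 9 and 9 (an assumption; the split is not given), the upper 95% limit of each SD is 1.916 times its estimate. Then n = 8.50 × 1.916² = 31.2, so 32 per group, still far below 78.

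**4. What 78 per group means if the stated SDs hold.**

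- Power for 4 h is above 99.99%; for 2 h it is 98.8%.
- Smallest observed difference reaching p < 0.05: 1.96 × √(17.345 / 78) = 0.92 h, under a quarter of the stated 4 h.

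**5. One possible source of 78 (conjecture only).** Suppose again 9 pilot patients per group, and that 2.21 and 3.53 were standard errors rather than SDs. The SDs would then be √9 = 3 times larger and the formula would give 8.50 × 9 = 76.5. An exact t test would need 78 (power 0.797 at 77 and 0.802 at 78). Nothing in the article says this, but under that reading power for 4 h would be about 80%, not nearly 100%.

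**6. Dropout step, taking 78 as given.**

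- 78 × 1.15 = 89.7, which matches the stated 90.
- To retain 78 after 15% loss: 78 / 0.85 = 91.8, so 92 per group (184 in total).
- 90 × 0.85 = 76.5 completers, 1.5 below 78. Ninety per group covers a loss of 1 − 78/90 = 13.3%.

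**The case against.** The error is in the safe direction. On the stated inputs the primary test has more than enough power, and no endpoint, analysis or allocation changes. It could therefore be called a reporting defect. That is fair as far as enrolment goes. But the figure is the trial's whole case for its size and is off by a factor of nine. The safe direction also depends on the pilot SDs being correct, which the figure of 78 itself puts in doubt.

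The consequences are conditional. Near-certain power and significance at about 0.9 h hold only if SDs from an 18-patient pilot carry over to a three-centre trial. With an SD of 8.9 h, 78 is right for 4 h. Both readings cannot be true, and this stands as a limit on what can be concluded.

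The dropout and labelling points are minor, and this also stands. The gap between 90 and 92 per group is small and makes no difference to power on the stated SDs. Section 2.15.2 moreover plans an intention-to-treat analysis with missing values filled in, so dropouts would remain in the main analysis. The value 0.84 is correct for 80% power; only its subscript is wrong. Both belong in the same correction and are not separate material errors.

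Finally, a rule for reading the confidence interval against 4 h would not repair the arithmetic and is a matter of preference. It is not requested here.

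**Conclusion.** The concern holds. The printed formula and inputs give 8.50, or 9 patients per group (10 with an exact t test), against the stated 78. The SDs agree between the Introduction and section 2.15.1, so a misprint confined to one place is unlikely, and nothing else in the article explains 78.

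The stated 80% power for 4 h therefore does not describe this trial on its own figures. If the pilot SDs hold, power is practically 100%. If 78 is the correct result, the calculation used a difference near 1.32 h, a common SD near 8.9 h, or some other unreported basis. The article does not allow a choice between these.

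The mismatch of 9 and 78 rests only on printed numbers. The pilot-imprecision figure of 32 and the standard-error conjecture also assume 9 pilot patients per group. The mislabelled quantile and the shortfall of 1.5 completers per group are correct but secondary.

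**What to change.** Keep 180 patients and rewrite the paragraph in section 2.15.1:

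1. Check against the pilot data whether 2.21 and 3.53 are SDs. Then either state the inputs that really give 78 (for example a difference of 1.32 h, or a common SD of 8.9 h) and their source, or state that the formula gives 9 per group and say why 180 are enrolled. If the pilot figures prove to be mislabelled, correct the Introduction as well.
2. Relabel the second quantile Z(1−β).
3. If 78 is kept as the target, state that 90 per group allows about 13% dropout, or that 15% dropout leaves about 76 per group.

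The cost is a look at the pilot data and the rewording of one paragraph. Enrolment, randomisation and the planned analysis do not change.
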